### Statistical analysis

Data from the demographic data collection and the outcome parameters will be cleaned blindly from the treatment data. Data are presented as mean scores with 95% confidence intervals. Linear regression analysis will be performed if data are not normally distributed.

A blinded evaluation of the trial patient’s functional status will be performed by a research assistant by use of the PRWE and qDASH scores. Blinded radiographic evaluation will be performed the intervention group and the control group. An independent expert will assess the degree of dislocation on an X-ray, blinded from the first assessment. Final blinded analysis of the primary outcome parameters will only be performed after 6-month follow-up.

The analysis of this study will be carried out according to the intention-to-treat principle, i.e. the patients will remain in the group they will be randomly allocated to at the baseline. Analysis of functional outcome will be assessed using repeated-measures analysis of variance (GLM 4) with the time as the within-group factor and the treatment as the between-group factor. The post hoc analysis will be performed on the time of randomisation. Group comparisons at different time points will only be made when the overall repeated-measures tests are statistically significant. All scores will be tested for normality using the Kolmogorov–Smirnov test. Parametric variables will be compared using the Student’s *t*-test, while non-parametric and ordinal variables will be compared using the Mann–Whitney *U* statistic. Nominal variables will be compared across independent groups using the chi-squared test or Fisher’s exact test. Homogeneity of variance will be assessed using Levene’s test.

Baseline characteristics that will be analyses are gender, age, dominancy, fracture side, fracture characteristics, smoking and osteoporosis. The outcome will be tested for normality and according to the outcome mean or median baseline characteristics will be compared.

Primary and secondary outcome measures are functional outcome (PRWE and qDASH), return to work, range of motion, pain, radiological outcome, complications and cost-effectiveness.

Missing data of the PRWE and qDASH score during follow-up can be imputed using multiple imputation based on baseline characteristics

The PRWE questionnaire will measure the primary outcome (PRWE after 6-month follow-up). In this questionnaire, pain and function are scored on a 0 to 10 scale. The total score can range between 0 and 100, with 0 being the best possible outcome and 100 the worst. The outcome will be tested for normality, and according to the outcome mean or median PRWE after 6 months will be calculated. The mean or median outcome after 6 months in the intervention group (e.g. 1 week of brace immobilisation) will be compared with the control group (e.g. 3 weeks of cast immobilisation). A *t*-test will be used to compare the different outcomes. A *p* value of < 0.05 will be taken as a threshold of statistical significance. To check for clinically relevant results, we will compare the outcomes between the two groups to check whether this difference will reach the minimal clinically important difference of the PRWE of 11.5. Different variables will be compared between the two treatment groups (e.g. 1 week of brace and 3 weeks of cast immobilisation groups). In addition, if possible, a multivariate analysis will be performed, to compare different secondary outcomes to the period of brace or cast immobilisation. Depending on the amount of missing data, we will impute outcomes using multiple imputation based on age, sex, smoking and fracture characteristics. For all analysis, SPSS statistical software (version 28.0) will be used, in which two-tailed *p* value < 0.05 will be considered significant.

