This study was initiated to assess whether a period of 1 week of brace immobilisation within non- or minimally displaced DRFs is safe and will lead to an equal functional outcome, earlier return to work, higher patient satisfaction and reduction of health care costs compared to 3 weeks of cast immobilisation. The hypothesis of the study is that 1 week of brace immobilisation is non-inferior to 3 weeks of cast immobilisation.

This randomised controlled trial will provide level 1 evidence on the optimal period and way of immobilisation for non- or minimally displaced distal radius fractures in adult patients. Literature indicates that a shorter period of immobilisation and immobilisation by bracing is safe and might even be beneficial.

This study protocol is based on the ‘DR PIP II: Distal Radius Plaster Immobilization Period II’ study protocol (NL62861.029.17) where 4 weeks versus 6 weeks of cast immobilisation is analysed within displaced and reduced DRFs [21].

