### Sample size calculation

The primary outcome will be the PRWE score at 6-month follow-up, of which the minimal clinically important difference is 11.5 points. To be conservative, we use a non-inferiority limit of 10.0. The SD of the PRWE is 14.0 [35]. With a power (1 − *β*) of 90% and a type I error (*α*) of 5%, a sample size of 34 patients per treatment group was calculated.

To allow a 10% drop-out, 74 patients will be included, 37 patients per treatment arm. We expect that all patients can be included within 1–1.5 year.

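### The rules for the primary PRWE comparison contradict each other, and the median/Mann–Whitney route among them cannot test the 10-point mean margin

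*Protocol article*

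**What the plan says.** The Background section states the aim: "The hypothesis of the study is that 1 week of brace immobilisation is non-inferior to 3 weeks of cast immobilisation". The Sample size calculation section fixes the endpoint ("The primary outcome will be the PRWE score at 6-month follow-up"), the margin ("To be conservative, we use a non-inferiority limit of 10.0") and the spread ("The SD of the PRWE is 14.0"), and arrives at 34 per group for 90% power and a 5% type I error. All of this is on the scale of a difference in means.

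The Statistical analysis section then gives these instructions:

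- Results are presented as means with 95% confidence intervals.
- "Linear regression analysis will be performed if data are not normally distributed".
- All scores go through a Kolmogorov–Smirnov test. Parametric variables get a t-test, while "non-parametric and ordinal variables will be compared using the Mann–Whitney" statistic.
- For the primary outcome, normality is tested and "according to the outcome mean or median PRWE after 6 months will be calculated". That mean or median is then compared between arms.
- Directly afterwards, a t-test is named for the comparison, with no condition attached.
- Significance is two-tailed p < 0.05. The observed difference is checked against the minimal clinically important difference of 11.5, not against 10.0.

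**The concern.** If the 6-month PRWE is not normal, an analyst following this section can defend three analyses: a linear regression, a Mann–Whitney test with medians, or a t-test. They do not answer the same question. The margin is a number of PRWE points on a mean difference. Mann–Whitney tests whether the two distributions are equal and yields no mean difference to set beside 10.0. A median difference is a different quantity, and it can be small when the mean difference is large. If a preliminary test on the trial's own data selects between mean and median, the quantity being estimated is not fixed in advance.

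At stake is the primary conclusion. A non-significant Mann–Whitney result, or two similar medians, could be reported as support for non-inferiority although neither tests it. The risk is greatest if harm from early mobilisation falls on a minority of patients.

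**Working it through.** **1. The plan's own figure, and its scale.** Inputs from the Sample size calculation section: margin Δ = 10.0, SD σ = 14.0, power 90%, type I error 5% (sidedness not stated). The true difference is taken as 0.

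n per group = 2σ²(z₁₋α + z₁₋β)² / Δ²

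- One-sided 5%: 2 × 196 × (1.645 + 1.282)² / 100 = 33.6, so **34**. This matches the plan.
- One-sided 2.5% (upper limit of a 95% CI): 2 × 196 × (1.960 + 1.282)² / 100 = 41.2, so **42**.

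The 34 per group is therefore a calculation for a mean difference whose 90% CI upper limit is held against 10.0.

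**2. Power by CI level.** SE = 14 × √(2/n), which is 3.40 at n = 34 and 3.25 at n = 37. The normal approximation is Φ(10/SE − z); the t-based figure uses the noncentral t distribution.

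| n per group | 90% CI: normal / t-based | 95% CI: normal / t-based |
|---|---|---|
| 34 | 90.3% / 89.8% | 83.8% / 82.7% |
| 37 | 92.3% / 91.9% | 86.7% / 85.8% |

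**3. Which routes keep the mean scale.**

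| Route in the text | Estimates the mean difference? | Compared with 10.0 as written? |
|---|---|---|
| t-test | Yes | No (two-tailed p against zero; difference checked against 11.5) |
| Linear regression on treatment | Yes | No |
| Medians / Mann–Whitney | No | No, and it cannot be |

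Regression on treatment alone reproduces the t-test. On one simulated data set both gave a difference of 2.12, p = 0.465 and a 90% CI upper limit of 6.94. It also rests on the same error assumptions as the t-test, so it is no remedy for non-normality.

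**4. How often normality would be rejected.** The article gives neither an expected PRWE mean nor a shape, so this is an assumption shown over a range: gamma scores, SD 14, capped at 100, both arms of 34 pooled, test at 5%.

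| Assumed mean | Lilliefors form | Uncorrected Kolmogorov–Smirnov |
|---|---|---|
| 8 | about 100% | about 100% |
| 12 | about 100% | about 92% |
| 16 | about 95% | about 40% |
| 20 | about 77% | about 14% |
| 30 | about 40% | about 2% |

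The article does not say which form is meant.

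**5. What the median/Mann–Whitney route can miss.** Assume that 25% of brace patients score 40 points worse and the rest are unaffected. The true mean difference is 0.25 × 40 = 10, exactly the margin. Control scores are gamma, 34 per arm.

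- Control SD 10, control means 10, 14, 20: Mann–Whitney is non-significant in 59%, 58% and 58% of trials. The upper limit of a rank-based (Hodges–Lehmann) interval lies below 10 in 51%, 43% and 35%. The mean-based limit at one-sided 5% wrongly declares non-inferiority in 5.9%, 6.6% and 6.3%.
- Control SD 14, control means 8 to 20: Mann–Whitney is non-significant in about 61–63%. The mean-based 95% CI wrongly declares non-inferiority in about 3%.

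**6. Whether skew alone requires a switch.** With gamma scores in both arms, SD 14 and control means 10 to 30, the ordinary mean-based limit at one-sided 5% has a type I error of 4.1–5.1% and power of about 89–90%. No switch is needed to protect the error rate.

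**The case against.** Several points on the other side are sound.

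- **Linear regression.** A reader might infer that every fallback abandons the margin. That is wrong: the regression coefficient for treatment is the mean difference, and its CI can be set against 10.0. What stands is that the stated trigger is wrong and that the sentence conflicts with the Mann–Whitney rule in the same section.
- **Mann–Whitney.** A reader might infer that the primary outcome will be analysed this way. The document does not establish it. The Mann–Whitney sentence is a general rule, and the only test named in the primary-outcome paragraph is an unconditional t-test. The fair reading is a contradiction, not a clear switch.
- **Cause.** The normality test is not what detaches the analysis from the margin. With perfectly normal data the written criterion would still be two-tailed p < 0.05 and a check against 11.5.
- **Likelihood.** A reader might infer that the median branch is the one most likely to be used. That holds only for low assumed means or the Lilliefors form; at mean 20 the uncorrected test rejects in about 14% of trials.
- **Rank methods are not always the weaker choice.** When gamma scores differ by 10 in mean with no harmed subgroup, Mann–Whitney is non-significant in only about 1–13% of trials and the t-test in about 16–18%. A rank-based limit also had higher power there. The loss in step 5 depends on harm being concentrated in a minority.

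It can also be said that an article condenses a fuller plan. That excuses missing detail, but not conflicting instructions on the primary comparison.

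**Conclusion.** The point holds as a contradiction over the primary analysis that should be corrected. The section lets a normality test choose between mean and median PRWE and gives three incompatible instructions for non-normal scores. One of them, medians with Mann–Whitney, cannot test non-inferiority against a margin on the mean scale.

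That the routes conflict, and that this one cannot test the margin, follows from the text and needs no assumption. The size does. In the assumed scenario of a 10-point mean harm carried by a quarter of brace patients, Mann–Whitney fails to flag a difference in about 58–63% of trials, whereas a mean-based limit wrongly declares non-inferiority in about 3% (95% CI) to 6–7% (90% CI). The article does not say that a non-significant result would be read as non-inferiority, so the 58–63% measures exposure to a wrong reading, not a predicted error rate. How often the branch would be triggered cannot be settled from the article.

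Removing the normality test is necessary but not sufficient, because the remaining t-test also lacks a comparison with 10.0.

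**What to change.** For the primary outcome, delete the normality-dependent choice and the sentence that makes non-normality the trigger for linear regression. State one analysis: the difference in mean 6-month PRWE, brace minus cast, from a t-test or a linear regression with an unequal-variance standard error. Add a bootstrap CI as a sensitivity analysis for skew. Conclude non-inferiority only if the upper confidence limit is below 10.0. Keep medians as description and Mann–Whitney for secondary ordinal variables.

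State a CI level that agrees with the sample size, in one of two ways:

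- a 90% CI (one-sided 5%), which fits the 34 per group at about 90% power; or
- a 95% CI, with the stated power restated to about 83% at 34 per group (about 86% at 37). Keeping 90% power with a 95% CI would need 42 per group, or 42 / 0.9 = 46.7, so 47 per arm with 10% drop-out.

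Cost: a change of wording and, if the 95% CI is chosen without enlarging the trial, a less favourable stated power.

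### Unless scores are imputed, the repeated-measures ANOVA uses completers only and, read literally, gates the 6-month PRWE comparison; the optional imputation omits treatment arm and observed PRWE

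*Protocol article*

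**What the plan says.** All of the following is in the protocol article.

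- **Endpoint** (Sample size calculation): "The primary outcome will be the PRWE score at 6-month follow-up". The non-inferiority limit is 10.0, the SD 14.0, power 90% and type I error 5%. This gives 34 per arm, raised to 37 per arm for 10% drop-out.
- **Model for functional outcome** (Statistical analysis): "Analysis of functional outcome will be assessed using repeated-measures analysis of variance (GLM 4"; the factors are given in the same sentence: "repeated-measures analysis of variance (GLM 4) with the time as the within-group factor and the treatment as the between-group factor". The same section names PRWE and qDASH as the functional outcomes, so the primary variable is covered.
- **Gate** (same section): between-group comparisons at individual time points are made only if the overall repeated-measures tests are significant.
- **Comparison of 6-month PRWE** (later in that section): "A *t*-test will be used to compare the different outcomes".
- **Analysis principle**: "intention-to-treat principle, i.e. the patients will remain in the group they will be randomly allocated to at the baseline".
- **Missing data**, stated twice: "Missing data of the PRWE and qDASH score during follow-up can be imputed using multiple imputation based on baseline characteristics", and "Depending on the amount of missing data, we will impute outcomes using multiple imputation based on age, sex, smoking and fracture characteristics".

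Questionnaires are completed at the emergency department (ED), at 6 weeks and at 6 months. PRWE is listed as an outcome at 6 weeks and 6 months only, and the ED forms are described as baseline data.

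**The concern.** Classical repeated-measures ANOVA needs a complete row for each patient. If nothing is imputed, a patient with an observed 6-month PRWE leaves the model because an earlier form is missing. On its own that would concern a supporting analysis. The gate makes it matter more, because it lets the completer model decide whether the 6-month comparison is made, and the text does not exempt the primary endpoint.

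Imputation could repair this, but not as described. It is discretionary, with no stated trigger, and the listed predictors leave out the two most important variables: treatment arm and the patient's own PRWE at other visits. In a non-inferiority trial, omitting arm is not a neutral simplification. It makes the arms look more alike, and likeness is what the trial sets out to show.

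**Working it through.** **1. Reproduce the sample size.** With margin 10, SD 14, true difference 0, one-sided 5% and 90% power:

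n per arm = 2 × (1.645 + 1.282)² × 14² / 10² = 33.6, rounded up to 34. This matches the article. One-sided 5% is kept below because it is the level that gives 34. The calculation is a single comparison at 6 months.

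**2. Completers per arm out of 37.** The 10% loss at 6 months is the article's allowance. The missing fraction m on each other form is my assumption (5–10%, independent between visits).

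Completers = 37 × 0.90 × (1 − m)^(k − 1), where k is the number of time levels (2 for 6 weeks and 6 months, 3 if the ED form is also a level).

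**3. Power of a two-group comparison at 6 months on those completers**, margin 10, SD 14, one-sided 5%. This stands in for the ANOVA, which does not itself test against a margin.

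| Scenario | Completers per arm | Power, noncentral t | Power, normal approximation |
|---|---|---|---|
| Planned 10% loss only | 33.3 | 89.2% | 89.8% |
| plus 5%, two levels | 31.6 | 87.8% | 88.4% |
| plus 10%, two levels | 30.0 | 86.2% | 86.9% |
| plus 5% on each, three levels | 30.1 | 86.3% | 87.0% |
| plus 10% on each, three levels | 27.0 | 82.8% | 83.6% |

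On the normal approximation, a likelihood-based mixed model gives 90.1% to 91.3% across the rows with only the planned loss or with 5% or 10% extra on both other forms. This assumes compound symmetry with correlation 0.3 to 0.7 and three time points. With only the planned loss, the gain over 89.8% is 0.3 to 1.5 points. The t-test on available 6-month scores stays at 89.8% in every row, because it needs no other form.

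**4. Imputing without treatment arm.** Suppose a fraction m of 6-month scores is missing at random in both arms and the listed predictors carry no information (assumed, the unfavourable end). Imputed values in both arms then centre on the pooled mean. Each arm mean becomes (1 − m) × own mean + m × pooled mean, so

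estimated difference = (1 − m) × true difference.

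At the limit (true difference 10), m = 10% gives 0.90 × 10 = 9.0 and m = 20% gives 0.80 × 10 = 8.0. Simulation with 37 per arm, SD 14 and one-sided 5% agrees: the estimates average about 9.0 and 8.0. False non-inferiority rises from about 5% with available cases to about 7% and about 9%.

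**5. Selective loss.** In an illustrative simulation, about 10% dropped out depending on the 6-week score, in opposite directions in the two arms. Completer bias was 0.8 to 1.9 PRWE points (correlation 0.3 to 0.7). A likelihood-based estimate using the 6-week score had bias near 0. The t-test on available 6-month scores would share the completer bias here, since those patients have no 6-month score.

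**The case against.** Four points can be made on the other side.

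- **The t-test needs only the 6-month score.** This is correct. A reader might infer that the plan discards observed primary-endpoint data outright. It does so only if the ANOVA is the primary test or if its gate applies to the t-test. The text leaves that open, which is the defect.
- **Intention-to-treat is not contradicted.** A reader might infer that completer analysis breaks the principle announced in "The analysis of this study will be carried out according to the intention-to-treat principle". The article defines it only as staying in the allocated group, and deleting incomplete rows moves nobody between groups. What can be said is that randomised patients with observed outcomes could be left out.
- **Imputation is planned, so the ANOVA need not be a completer analysis.** This is also true, and a journal article may leave details to an analysis plan that is not shown. But the article does more than stay silent: it makes imputation optional and names a predictor list. Neither that list nor the article's list of baseline characteristics contains arm or any PRWE score.
- **The power loss is small.** This stands. With the planned loss alone it is about 1 point relative to a mixed model. The lower figures rest on missingness rates that the article does not give and on no imputation being done.

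**Conclusion.** The point holds as a weakness in how the analysis is fixed; the trial does not lose its planned power under its own assumptions. Three things are established from the text: a method that uses completers unless scores are imputed, a gate that literally places that method ahead of the 6-month comparison, and an optional imputation whose listed predictors omit arm and observed PRWE.

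The imputation model is the more serious part, because its error runs in the direction of the trial's hypothesis. A difference at the limit shrinks by 1 point with 10% missing and by about 2 with 20%, and false non-inferiority goes from 5% to about 7% and 9%. This assumes uninformative predictors and random missingness; predictors cannot stand in for arm, since randomisation makes them unrelated to it.

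The bias of 0.8 to 1.9 points from selective loss, against a limit of 10, needs drop-out that works in opposite directions in the two arms. It is an illustration only.

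**What to change.** 1. Replace the repeated-measures ANOVA and its gate with a linear mixed model for PRWE (and likewise qDASH) at 6 weeks and 6 months, using every observed score. Include treatment, visit, treatment-by-visit, baseline score and the sex and age strata.
2. Take the 6-month treatment difference and its confidence interval from this model as the primary result and compare them with the 10.0 limit. State what role, if any, the t-test keeps, and that no prior significant test is required.
3. If imputation is kept, fix in advance when it is used and include treatment arm and all observed PRWE scores in the imputation model. Done this way, it is an acceptable alternative to the mixed model for handling missing scores.

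The cost is wording and slightly more analysis work: no extra patients, visits or data, and the stated software fits mixed models. The mixed model also relies on data being missing at random, and it does not recover all the information lost when 6-month scores are missing.

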**Table 2 Tab2:**
[figure not shown]
SPIRIT figure

At each follow-up (FU) visit, the research coordinator or research assistant will ascertain patient status (i.e. secondary interventions, adverse events/complications, deaths) and will verify the information within medical records. All adverse events will be addressed to the principal investigator. The patients will be asked to indicate the actual pain level based on the VAS score, if they are currently treated by a physical therapist and if they returned to work. At 6 weeks and 6 months, the range of motion of the wrist will be measured using a goniometer.

Patients will be asked to complete questionnaires relating to disability (qDASH score and PRWE score) and medical consumption, productivity and general health to analyse cost-effectiveness (EQ-5D, iPCQ, iMCQ). Patients will be asked to complete the questionnaires at the ED as well, to generate baseline data.

Plain X-rays of the wrist will be made at the time of presentation in the hospital at the ED, after 6 weeks and 6 months. The X-ray at 6 months will be taken to determine the grade of degenerative joint changes. Time to define the presence of a delayed- or malunion will be at 6 months. Intention-to-treat principle will be maintained.

Both treatment options and used methods of treatment for this type of fracture are well known. Earlier research did not report any (serious) adverse events. All adverse events will be reported by the investigator; severe adverse events will be reported by the investigator to the sponsor of the study without undue delay after obtaining knowledge of the events. We performed an investigator-initiated risk classification: the risk of this study is expected to be negligible. Therefore, no DSMB/safety committee would be necessary. A monitoring audit will be conducted at the start of the study, after inclusion of the first 10 patients and after finishing the inclusion of patients. Also, a line listing of (serious) adverse events will be kept up and reported annually to the Amsterdam UMC Ethical Board.

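### The repeated-measures ANOVA treatment factor and the post hoc test at randomisation do not address 6-month PRWE, and they are not reconciled with the separately planned 6-month t-test

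*Protocol article*

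**What the plan says.** All references are to the protocol article.

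- **Target.** Sample size calculation: "The primary outcome will be the PRWE score at 6-month follow-up", and "we use a non-inferiority limit of 10.0". PRWE at 6 weeks, and qDASH at 6 weeks and 6 months, are secondary outcomes (Methods/design).
- **Model.** Statistical analysis: functional outcome, which that section identifies as PRWE and qDASH, goes into a repeated-measures ANOVA "with the time as the within-group factor and the treatment as the between-group factor".
- **Post hoc test.** Same paragraph: "The post hoc analysis will be performed on the time of randomisation". The next sentence allows comparisons at individual time points only if the overall repeated-measures tests are significant.
- **Time levels.** Follow-up text under Sample and selection criteria: "Patients will be asked to complete the questionnaires at the ED as well, to generate baseline data". The analysis section does not say whether this ED score is a level of the time factor.
- **Second analysis.** A later paragraph of Statistical analysis compares 6-month PRWE between the arms with a t-test at two-tailed p < 0.05 and checks the difference against 11.5 points. It does not mention the ANOVA.

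**The concern.** In a repeated-measures ANOVA the null hypothesis of the between-group factor is that the arms have the same mean score averaged over the time levels. The trial asks about one time only. Averaging mixes the 6-week score into the comparison, and also the ED score if that is a level. The ED score precedes treatment and cannot carry a treatment effect.

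The protocol itself expects faster recovery with shorter immobilisation, so unequal differences at 6 weeks and 6 months are plausible. An early benefit would offset a later harm in the averaged comparison. A difference at 6 weeks alone could make the factor significant although the arms are equal at 6 months.

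Read literally, the post hoc sentence does not repair this. Randomisation makes the arms equal in expectation at that moment, so a 5% test there rejects in about 5% of trials whatever the treatments do. If the ED score is not a time level, the model contains no score at that time to test.

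At stake is which result answers the trial question. Two analyses cover the primary outcome, they can disagree, and neither is ranked.

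**Working it through.** **Inputs from the Sample size calculation section.** Margin 10.0; "The SD of the PRWE is 14.0"; power "of 90% and a type I error" of 5%; "a sample size of 34 patients per treatment group was calculated".

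**Assumed, because the document gives no figure.** Within-patient correlation ρ = 0.3, 0.5 or 0.7 with compound symmetry; SD 14 at every time; complete data. The time factor has k = 3 levels (ED, 6 weeks, 6 months) or k = 2 (6 weeks, 6 months).

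**1. The plan's own figure.** n = 2(14/10)²(1.645 + 1.282)² = 33.6, so 34 per arm. This reproduces the stated number with a true difference of 0 and a one-sided 5% test. At one-sided 2.5% the calculation gives 42.

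**2. Direct 6-month t-test, 10-point difference.** SE = 14√(2/34) = 3.40; 10/3.40 = 2.95; power 82.7% at two-sided 5% with 34 per arm (85.8% with 37).

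**3. Treatment main effect.** It is equivalent to a t-test on each patient's mean over time:

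- difference = mean of the k time-specific differences
- SD of a patient mean = 14√[(1 + (k − 1)ρ)/k]
- SE = that SD × √(2/34)

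Harm of 10 points at 6 months only, ρ = 0.5:

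- k = 3: difference 10/3 = 3.33; SD 14√(2/3) = 11.4; SE 2.77; ratio 1.20; power 22%.
- k = 2: difference 10/2 = 5; SD 14√0.75 = 12.1; SE 2.94; ratio 1.70; power 39%.

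**4. Time-by-treatment test from the same ANOVA.** Noncentrality = (34/2) × Σ(dⱼ − d̄)² / [14²(1 − ρ)], where dⱼ is the difference at time j. For harm at 6 months only, k = 3, ρ = 0.5: the sum of squares is 66.7, so 17 × 66.7/98 = 11.6, and power is 86%.

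**5. Range over ρ = 0.3 to 0.7** (noncentral F, confirmed by simulation):

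| Brace minus cast, 6 weeks / 6 months | Main effect, k = 3 | Main effect, k = 2 | Time-by-treatment, k = 3 | Time-by-treatment, k = 2 |
|---|---|---|---|---|
| 0 / 10 | 19-26% | 35-44% | 72-98% | 69-96% |
| 10 / 10 | 58-76% | 88-95% | 72-98% | 5% |
| −5 / 10 | 8-10% | 12-15% | 93% to over 99% | 96% to over 99% |
| −10 / 10 | 5% | 5% | over 99% | over 99% |

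The direct 6-month t-test has 82.7% power in every row.

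**6. If the significance condition also governed the 6-month t-test.** For harm at 6 months only, the main effect and the t-test are both significant in 19-27% (k = 3) or 36-43% (k = 2) of simulated trials. If either overall test suffices, the t-test together with that condition succeeds in about 73-84% over all patterns examined.

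**7. The reverse pattern, 10 / 0.** By symmetry the main effect rejects in 19-26% (k = 3) or 35-44% (k = 2) and the time-by-treatment test in 69-98%, although the 6-month difference is zero. The time-by-treatment test therefore does not isolate 6 months either.

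**The case against.** The strongest reply is that the plan already contains the right comparison. The later paragraph of Statistical analysis names 6-month PRWE as primary and tests it with a t-test, which has 83% power for a 10-point difference. A reader might infer from the ANOVA paragraph alone that the trial never tests the 6-month difference, or that it would mostly miss a 10-point harm. The document supports neither inference.

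Four further points have weight:

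- An ANOVA with these two factors normally also gives the time-by-treatment test, and the protocol speaks of overall tests in the plural. That test detects a harm confined to 6 months in 69-98% of trials and the fully cancelling pattern in over 99%.
- With equal harm at both follow-ups on two levels, the main effect (88-95%) does better than the t-test.
- Rejecting when only the 6-week scores differ is not an error for the hypothesis that the ANOVA tests, since 6-week scores are secondary outcomes.
- The post hoc sentence may be no more than poor wording, and comparisons at different time points are mentioned straight after it.

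All of this stands, and it limits the size of the problem. Three things remain. The between-group factor and the post hoc test as written do not target 6 months. The t-test is neither named as the governing analysis nor exempted from the significance condition. And for 6-week PRWE and both qDASH outcomes, the ANOVA is the only analysis named specifically for functional outcome.

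**Conclusion.** The point holds in limited form. The treatment factor averages over time and the post hoc analysis sits where no treatment effect can exist, so neither answers the primary question. The 6-month t-test does compare the arms at the right time, but as a two-sided test of difference, and the text leaves its relation to the ANOVA open.

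The drop from 83% to 19-26% (three levels) or 35-44% (two levels) applies only if the main effect alone is relied on and the harm is confined to 6 months. It rests on 34 per arm, SD 14 at each time and assumed correlations of 0.3 to 0.7. It must not be quoted as the power of the trial or of the whole ANOVA.

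Nor would clarifying the ANOVA be enough. The sample size is built on a 10.0-point limit, yet the analysis section compares no confidence limit with it and refers only to 11.5.

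**What to change.** In the Statistical analysis section:

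1. Name one primary analysis: the brace-minus-cast difference in PRWE at 6 months, with the upper limit of its confidence interval compared with 10.0. State the confidence level; the 34 per arm corresponds to a one-sided 5% test. Word the ANOVA and t-test paragraphs so that they agree, and state that this comparison does not depend on an overall test being significant.
2. Replace the post hoc sentence with between-group contrasts at 6 weeks and 6 months.
3. Use the ED score as a covariate, not as a level of the time factor.
4. Describe the overall treatment factor as supportive.

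The cost is a few sentences. No extra patients, visits or data are needed, because the ED questionnaires are already planned, and the model can be fitted in the planned software. The downside is that the single overall treatment p-value is no longer a main result.
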